#### 1.4. Study population

The reference population will be pediatric patients treated in primary care with a clinical diagnosis of MC.

##### 1.4.1. Inclusion criteria

- Who are diagnosed with a MC infection (clinical diagnosis).

- Who are between the ages of two and six.

- Whose parents or guardians have provided written informed consent for participation.

##### 1.4.2. Exclusion criteria

- Immunocompromised patient (congenital or acquired).

- Patient has received other topical treatment within the last month.

- Patient has lesions on face, neck or genital area.

- Patient who, in the view of the attending physician, will not comply with treatment and/or scheduled visits.

#### 1.5 Informed consent

In accordance with Spanish law, parents/guardians must personally sign and date the latest approved version of the informed consent form before any study specific procedures are performed.

Written and verbal versions of the Participant Information Sheet and the Informed Consent Form will be presented to the participants (parents/guardians), detailing no less than: the exact nature of the study; the implications and constraints of the protocol; the known side effects and any risks involved in taking part. It will be clearly stated that the participant is free to withdraw from the study at any time for any reason without prejudice to future care, and with no obligation to provide the reason for withdrawal.

The participant will be allowed as much time as they wish to consider the information, and the opportunity to question the Investigator, their physician or other independent parties to decide whether they will participate in the study. Written informed consent will then be obtained by means of the participant's dated signature and the dated signature of the person who presented and obtained the informed consent. The person who obtained the consent must be suitably qualified and experienced, and have been authorized to do so by the Principal Investigator. A copy of the signed ICF will be given to the participants. The original signed form will be retained at the study site.

#### 1.6 Screening and eligibility assessment

All parents/guardians of patients diagnosed with MC will be provided the necessary written information for study enrollment (information sheet) as well as clarification of any questions they may have. Once the patient has been determined to be valid (fulfillment of inclusion/exclusion criteria and written informed consent), they will be assigned a randomization code. The baseline visit will be done and then the patient will be scheduled for the next visit. Each parent/guardian will receive precise instructions for how to apply the treatment and will receive a vial of their designated treatment solution coded with the patient's number. The patient will be scheduled for the four follow-up visits at 15, 30, 45 and 60 days from the first treatment application.

#### 1.7 End of trial assessment

Each study participant can leave the study for two reasons:

1) Loss to follow-up (before the end of follow-up protocol, without successful treatment).

a. Lack of efficacy.

b. Choice of the patient.

c. Adverse effects.

d. Loss to follow-up (missing scheduled visits).

e. Breaking the blind.

f. Other.

2) Completion of follow-up.

g. Attended all scheduled visits

h. Success of treatment

A completion form should be filled out for all patients, whether they have finished the study or not.

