**Methods/design:**

The study design is a double-blind, randomized clinical trial, using three types of topical treatment. The treatment consist of daily applications of potassium hydroxide (KOH) in aqueous solution at 10% and 15% concentration, and a placebo administered in the control group. Four follow-up visits (at 15, 30, 45 and 60 days) are planned to evaluate treatment effectiveness and patient tolerance.

The main outcome measure of the trial will be the healing rate, defined as lesion disappearance in the affected zones after the topic application of the experimental treatment. Secondary measures will be the principal characteristics and evolution of the affected zone (surface area, number of lesions, size and density of lesions), treatment tolerance (hyperpigmentation, itching, burning, pain), recurrence rate and the natural evolution of lesions in the control group.

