#### 1.3 Primary and secondary endpoints/outcome measures

Efficacy will be assessed in each of the areas detected in the previous visit. If there are new areas affected, they will be evaluated at the next visit (a description of the new lesion will be recorded in the topographic section of the patients record).

The principle efficacy variable (primary endpoint) will be calculated for each of the affected areas, as an indicator variable: (1. There is a lesion in the area/0. No lesion in the area) at 60 days from baseline. Each patient will be considered cured if they have no lesions in any of the treated areas.

Secondary efficacy variables (secondary endpoints) will be calculated for each location as follows:

- Number of lesions.

- Extent of area affected.

- Mean size of lesions.

○ < 0.5 cm.

○ 0.5 cm. - 1 cm.

○ > 1 cm.

- Efficacy of method: Ordinal scale with five categories.

○ Worsening (net increase in number of lesions or growth of existing ones).

○ No changes *(no modifications to the lesion).*

○ Slight improvement *(disappearance of up to 50% of lesions).*

○ Moderate improvement *(disappearance of more than 50% of lesions).*

○ Cure (*complete disappearance of lesions*) (primary endpoint).

- Digital photograph.

- Lesion density*: Number of lesions/Extent of affected area

*NOTE: If the parents locate new lesions between visits they should NOT treat them until the physician has clinically evaluated their topography*.

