#### 1.8. Statistical methods and sample size

##### 1.8.1. Statistical analysis

The statistical analysis will be carried out on several different samples of the study population. The valid or valuable patient group is defined as those patients that fulfill all the inclusion criteria, none of the exclusion criteria, whose parents have provided consent for their participation and who have been assigned a treatment (randomized code). The safety sample is defined as the group of valid patients who have received treatment in the study at least once, whether or not its effectiveness has been assessed (who came to at least one follow-up visit). The intention to treat (ITT) sample is defined as the group of valid patients who have received treatment at least once and who have been assessed for its effectiveness at least once. The per protocol (PP) sample is defined as the group of patients that make up the ITT sample, have been assessed for efficacy and have not violated the protocol in any of the following ways:

- Violation of blinding.

- Greater than 10% missed treatments.

- Loss to follow-up by missing a scheduled visit.

The unit of analysis is the patient. Nevertheless, each patient can present multiple affected areas. An area is considered to be a set of lesions whose perimeter does not coincide with another affected area, with a single area being possible. No more than 15 affected areas per patient are expected.

A descriptive analysis of all the variables collected will be done, expressing quantitative variables as means, medians, minimums, maximums and standard deviations (SD), and categorical variables as frequencies and percentages.

The homogeneity of the study groups with respect to the following baseline parameters will be compared:

Demographic variables

Initial topography

Clinical history of associated diseases

History of treatments received (> 1 month)

To determine the existence of an association between a group and secondary efficacy variables at each period of follow-up, the single-factor ANOVA test will be used for quantitative variables (extent, number of lesions, etc.) and the chi-squared test will be used for categorical variables (cure).

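### Section 1.7 lets a child finish the study on cure before day 60, which conflicts with the day-60 primary endpoint, the by-visit analyses and the recurrence rate

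*Protocol article*

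**What the plan says.** Section 1.7 (End of trial assessment) opens with "Each study participant can leave the study for two reasons" and gives two routes.

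- Route 1 is "Loss to follow-up (before the end of follow-up protocol, without successful treatment", followed by reasons a to f.
- Route 2 is completion of follow-up, with two separate items: "g. Attended all scheduled visits" and "h. Success of treatment". No day is attached to the second.

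Other sections rely on observation up to day 60:

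- Section 1.3 (endpoints) fixes the primary endpoint "at 60 days from baseline. Each patient will be considered cured if they have no lesions in any of the treated areas". Section 1.8.2 sizes the trial on complete elimination at the final, 60-day visit.
- The Abstract names as secondary measures "recurrence rate and the natural evolution of lesions in the control group".
- Section 1.8.1 plans group comparisons at each follow-up period and a repeated-measures analysis of the quantitative efficacy variables.
- The per-protocol definition in section 1.8.1 excludes "Loss to follow-up by missing a scheduled visit".
- The Summary of trial design and section 1.6 schedule visits at 15, 30, 45 and 60 days for every patient.
- The Background says that further lesions may appear later because the virus may still be incubating.

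**The concern.** Listing success separately from full attendance adds nothing unless a cured child can complete without attending every visit. The qualifier in route 1 points the same way: leaving early with success is not a loss. On this wording a child clear at day 15, 30 or 45 may go unobserved at day 60.

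That would undermine three things. Day-60 status would be unknown in children cured early, and no scoring rule for them is stated. Recurrence can be seen only at visits after clearance, which are the visits such a child would skip. The later by-visit and repeated-measures comparisons would describe mainly children who are not cured. The gaps would be caused by the outcome itself and would be commoner in whichever arm clears more children. A later analysis plan can choose how to score a missing value, but it cannot recover an observation that was never made.

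**Working it through.** **Plan's own figure.** Inputs from section 1.8.2: cure 20% vs 70%, chi-squared test, 80% power, 5% significance (two-sided assumed), 20% loss. Without continuity correction this needs 15 evaluable per group, and 15 / 0.8 = 18.75, so 19. The stated 20 is reproduced to within one patient, so sample size is not the issue. With 20 × 0.8 = 16 evaluable per arm, power is 84.6%.

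**Assumptions.** The documents give neither the share of cures seen before day 60 (*e*) nor the relapse rate among those children (*r*). I take *e* = 25–75% and *r* = 0–30%, the same in every arm, and let every early-cured child leave. These values are illustrative only.

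**Who is missing.** Of 20 children per arm, 0.70 × 20 = 14 cures are expected on KOH and 0.20 × 20 = 4 on placebo. Multiplied by *e*, 3.5 to 10.5 KOH children and 1 to 3 placebo children would have no day-60 status.

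**Formulas**, with *p* = 0.70 or 0.20:

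- early clearance carried forward as cure: *p*
- true day-60 clearance: *p*(1 − *e r*)
- leavers dropped as missing: *p*(1 − *e*) / (1 − *p e*)

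| *e* | carried forward | true, *r* = 0 | true, *r* = 0.3 | leavers dropped |
|---|---|---|---|---|
| 0.25 | 70.0 vs 20.0 | 70.0 vs 20.0 | 64.7 vs 18.5 | 63.6 vs 15.8 |
| 0.50 | 70.0 vs 20.0 | 70.0 vs 20.0 | 59.5 vs 17.0 | 53.8 vs 11.1 |
| 0.75 | 70.0 vs 20.0 | 70.0 vs 20.0 | 54.2 vs 15.5 | 36.8 vs 5.9 |

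(Percent, KOH vs placebo.)

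**Direction.**

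- Carrying forward always reports a 50-point difference. The true difference is 0.50(1 − *e r*), which falls to 0.50 × (1 − 0.225) = 38.7 points in the last row. With any relapse, this rule favours KOH.
- Dropping leavers puts the KOH rate below its true value in every row. With no relapse, the difference is also too small: 47.8, 42.7 and 30.9 points against 50. With 30% relapse, the true differences are 46.2, 42.5 and 38.7 points, so the first two rows come out about level and the last is still too small.

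**Power on true day-60 status**, 16 evaluable per arm: 84.6% with no relapse, down to 64.5% at *e* = 0.75 and *r* = 0.3.

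**The one timing figure in the document.** The Background cites a mean treatment period of 54 days in the study behind the 70% and 20%. If that is the mean among cured children who clear at the visits, the early share is largest when all early cures fall at day 45: 60 − 15*e* = 54, so *e* = 6/15 = 40% at most. If it includes 30% uncured children treated to day 60, 60 − 15 × 0.7*e* = 54, so *e* = 6/10.5 = 57% at most. The text does not say which. At *e* = 40% and *r* = 10–30%, the true difference is 0.50 × 0.96 = 48 to 0.50 × 0.88 = 44 points.

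**The case against.** The strongest reply is that no sentence discharges a cured child. The Summary of trial design plans five appointments and section 1.6 books all four follow-up visits for everyone. Items a to h could be codes for the completion form, with h recording an outcome. The reference to remaining cases at day 60 in the Summary of trial design does not settle this, because it follows a sentence about missed visits. This part stands: early exit is something the wording permits, not something it orders. The wording still gives success as a way to complete without full attendance, and nothing requires a cured child to return.

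A reader might infer four stronger points that the documents do not support:

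- *Early successes would be removed from the per-protocol sample.* Section 1.7 files success under completion and confines loss to exits without success, so an early success can be read as a completer. The cross-reference is unclear, but a collision is not shown.
- *The bias favours KOH.* This holds only if early clearance is carried forward. No scoring rule is stated, and dropping leavers understates the KOH rate.
- *Three quarters of cures would come before day 60.* This has no source and sits poorly with the 54-day figure. It serves only as the upper end of a range.
- *Keeping all visits makes recurrence fully observable.* A child first clear at day 60 has no later visit. Recurrence is also named only in the Abstract, and its definition may sit in the full protocol.

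The time-to-cure analysis is not harmed by exit at cure.

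**Conclusion.** The point holds as a conflict between stated rules. Section 1.7 permits exit on success before day 60, while the primary endpoint, the by-visit analyses and the recurrence rate need the visits that follow. The reading is an inference from the structure of 1.7, though a strong one. The resulting gaps would be outcome-dependent and unequal between arms.

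The size cannot be fixed from the document. Across the assumed ranges, the reported KOH rate could be anywhere from about 37% to 70%, depending on an unstated scoring choice and on how many cures come early. The lower end relies on a 75% early share, above what either reading of the 54-day figure allows. This should be fixed, and before enrolment, because observation that has stopped cannot be restored. It does not show that the trial's result would be biased in a known direction.

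**What to change.** In section 1.7, state that success of treatment is recorded as an outcome and does not end follow-up. Then:

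- keep every cleared child on the scheduled 15, 30, 45 and 60-day visits;
- score the primary endpoint on day-60 status for all children;
- count recurrence as a lesion at a later visit in a child recorded clear earlier, and say that it cannot be observed in children first clear at day 60;
- state in section 1.8.1 that an early success is not in itself a per-protocol violation.

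This concerns observation only and says nothing about treatment after clearance. An alternative that also reconciles the text is to redefine the endpoint as cure by day 60 and drop or redefine recurrence, but that changes the question and leaves relapse unseen.

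The cost is a change of wording and a few more visits by cleared children. The visits are already in the schedule, and the sample size stays at 20 per group.

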#### 1.8. Statistical methods and sample size

##### 1.8.1. Statistical analysis

The statistical analysis will be carried out on several different samples of the study population. The valid or valuable patient group is defined as those patients that fulfill all the inclusion criteria, none of the exclusion criteria, whose parents have provided consent for their participation and who have been assigned a treatment (randomized code). The safety sample is defined as the group of valid patients who have received treatment in the study at least once, whether or not its effectiveness has been assessed (who came to at least one follow-up visit). The intention to treat (ITT) sample is defined as the group of valid patients who have received treatment at least once and who have been assessed for its effectiveness at least once. The per protocol (PP) sample is defined as the group of patients that make up the ITT sample, have been assessed for efficacy and have not violated the protocol in any of the following ways:

- Violation of blinding.

- Greater than 10% missed treatments.

- Loss to follow-up by missing a scheduled visit.

The unit of analysis is the patient. Nevertheless, each patient can present multiple affected areas. An area is considered to be a set of lesions whose perimeter does not coincide with another affected area, with a single area being possible. No more than 15 affected areas per patient are expected.

A descriptive analysis of all the variables collected will be done, expressing quantitative variables as means, medians, minimums, maximums and standard deviations (SD), and categorical variables as frequencies and percentages.

The homogeneity of the study groups with respect to the following baseline parameters will be compared:

Demographic variables

Initial topography

Clinical history of associated diseases

History of treatments received (> 1 month)

To determine the existence of an association between a group and secondary efficacy variables at each period of follow-up, the single-factor ANOVA test will be used for quantitative variables (extent, number of lesions, etc.) and the chi-squared test will be used for categorical variables (cure).

In the case that the ANOVA cannot be used because a quantitative parameter does not fulfill the application criteria (non-normality/heteroscedasticity) the data will be transformed (logarithmic) from the original parameter, or a non-parametric analog test (Kruskal-Wallis) will be used. In all 2 × 2 comparisons (Group I, II vs. Placebo), the significance level will be adjusted for multiple comparisons.

The evolution of the quantitative efficacy parameters will also be assessed, by group, for the different time periods, using a repeated measures analysis.

The relationship between the baseline variables and the efficacy variables will be assessed at the end of the study, and in the case that an association is found, a multivariate analysis will be carried out to assess possible confounding factors of the group effect on adjusted efficacy: a multiple regression analysis will be used in the case of quantitative efficacy variables and a multinomial regression will be used in the case of qualitative variables.

The time from treatment to cure will be calculated as the difference between the date of first treatment and the disappearance of lesions or the end of the study (treatment initiation). Survival tables and the Kaplan-Meier statistic will be calculated to compare cure times between the different treatment groups. In the case that associations are found between efficacy variables and baseline conditions, a Cox proportional risk model will be adjusted.

Data analysis will be by ITT, by protocol and by safety sample.

In all cases a p-value below 0.05 will be considered significant.

Data will be analyzed using the statistical package "R": http://www.r-project.org.

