### Trial design

#### 1.1 Summary of trial design

The study will be a double blind clinical trial with random treatment allocation. Patients will be randomized into three parallel treatment arms. Treatment will consist of the application of topical 10% or 15% KOH in an aqueous solution for the two treatment groups, compared to a placebo-treated control group.

A total of five appointments are planned, one baseline and four follow-up visits. Screening will be done during the baseline visit to verify that all patients fulfill the inclusion and exclusion criteria, and have signed a written consent form, in addition to recording sociodemographic variables and a clinical history.

The efficacy of and tolerance to the treatment, as well as the appearance of new lesions, concomitant treatments and adverse affects will be evaluated in the follow-up visits.

During the baseline visit, the patient will be diagnosed and essential information will be recorded (inclusion/exclusion criteria, sociodemographic variables and clinical assessment). All valid/evaluable patients will be assigned a randomization code, up to a maximum of 60 patients who fulfill the inclusion/exclusion criteria. Neither the patient, their parents, nor the pediatrician will know to which group the patient has been assigned. Four follow-up visits are planned, at 15, 30, 45 and 60 days (± 3 days) from baseline. Each visit will include a clinical assessment, where the appearance of new lesions will be recorded. The efficacy of treatment and the tolerance of treated lesions since the last visit will be studied. A photograph of the affected area will be taken. If the patient misses the follow-up visit, compliance will be noted in the completion worksheet (which will be filled out in all remaining cases at 60-day follow-up). The randomization code will be revealed if the attending physician believes this to be appropriate. In this case the patient will be removed from the study, filling out the completion worksheet.

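### The safety, ITT and per-protocol samples all admit only children who meet every eligibility criterion, so a treated child later found ineligible belongs to no analysed sample

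*Protocol article*

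**What the plan says.** Section 1.8.1 of the protocol article first defines a parent group: "The valid or valuable patient group is defined as those patients that fulfill all the inclusion criteria, none of the exclusion criteria". The same sentence adds parental consent and an assigned code as further conditions. Each analysis sample is then built from that group.

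- **Safety:** "The safety sample is defined as the group of valid patients who have received treatment in the study at least once". A clause follows: "whether or not its effectiveness has been assessed (who came to at least one follow-up visit".
- **ITT:** "The intention to treat (ITT) sample is defined as the group of valid patients who have received treatment at least once", with at least one assessment of effectiveness also required.
- **Per protocol:** members of the ITT sample without any of three violations, namely broken blinding, more than 10% of treatments missed, or a missed scheduled visit.

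The end of the statistical analysis section names these three samples as the basis of analysis and no others.

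On sequence, section 1.1 (Summary of trial design) says: "Screening will be done during the baseline visit to verify that all patients fulfill the inclusion and exclusion criteria". Section 1.6 says that once validity has been determined, "they will be assigned a randomization code. The baseline visit will be done and then the patient will be scheduled for the next visit".

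**The concern.** A safety sample should contain everyone exposed to study solution, and an ITT sample should follow the randomization. Here both carry an eligibility condition with no date attached. If a breach comes to light after treatment has started, the literal definition takes the child out of the safety, ITT and per-protocol samples together. Two things are then at stake:

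- an adverse event in an exposed child has no sample in which to be reported;
- the arms being compared are no longer simply those formed by randomization.

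Breaches of this kind can plausibly surface late. A recent topical treatment may be mentioned only at follow-up. The diagnosis is clinical, and the Background lists viral verrucas and insect bites in the differential diagnosis.

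**Working it through.** **1. Which sample holds the child?** Take a child with consent, a code and at least one application, who is later found to have had another topical treatment within the last month (an exclusion in section 1.4.2).

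- Parent group: fails, because one exclusion criterion is met.
- Safety: fails, because it is restricted to the parent group.
- ITT: fails for the same reason.
- Per protocol: fails, because it is a subset of ITT.

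The child is in no analysed sample.

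**2. Does the eligibility condition do any work?** Section 1.8.1 lists meeting the criteria and holding a code as separate, cumulative conditions. If every coded child counted as valid by construction, the eligibility wording would be redundant. The term is also used unevenly: in section 1.6 validity comes before the code, while in section 1.8.1 it includes the code. The per-protocol violations, where an eligibility breach would usually appear, do not mention it. Eligibility therefore acts only at the parent group, where it affects safety and ITT as well.

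**3. The plan's own sample size (section 1.8.2).** Inputs are 20% and 70% cure, 80% power, 5% significance (two-sided assumed) and 20% loss. With pooled proportion 0.45 and no continuity correction:

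n = [1.96·√(2·0.45·0.55) + 0.842·√(0.2·0.8 + 0.7·0.3)]² / 0.5² = 14.3, so 15 per group.

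15/0.8 = 18.75, so 19. The stated 20 is reproduced to within one patient. Under the same formula, power is 0.92 with 20 per arm, 0.89 with 18 and 0.85 with 16. Losing one or two children is not mainly a power problem.

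**4. How likely is at least one such child?** The documents give no rate of late-discovered ineligibility, so q is assumed. Among 60 children the expected number is 60q and the chance of at least one is 1 − (1 − q)^60.

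| Assumed q | Expected children | Chance of at least one |
|---|---|---|
| 1% | 0.6 | 45% |
| 2% | 1.2 | 70% |
| 5% | 3 | 95% |
| 10% | 6 | 99.8% |

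**5. What one or two children do (counts are illustrations).**

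- Safety, 20 treated per arm: one affected child removed takes 1/20 (5%) to 0/19 (0%); two take 2/20 (10%) to 0/18 (0%).
- Cure on KOH, 16 evaluable (20 × 0.8): 11/16 = 68.8%. Removing two uncured children gives 11/14 = 78.6%. Removing two cured children gives 9/14 = 64.3%.
- Contrast with placebo at 3/16 (18.8%): the difference is 68.8 − 18.8 = 50.0 points. Remove 40% of non-responders in both arms (2 of 5, and about 5 of 13) and it becomes 11/14 − 3/11 = 78.6 − 27.3 = 51.3 points. Remove two placebo non-responders only and it becomes 11/16 − 3/14 = 68.8 − 21.4 = 47.3 points (from unrounded rates).

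The direction of any distortion depends on who is removed and from which arm.

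**The case against.** The strongest reply is that *valid* describes status when the code was issued. Section 1.6 makes the determination of validity a precondition of the code, and the design summary gives codes only to children who fulfil the criteria. No section describes re-judging eligibility afterwards, and the exit reasons in section 1.7 do not name ineligibility except through the residual category of other reasons. This reading is possible, and it means that removal is a consequence of the literal wording, not a stated procedure. It does not settle the matter, because the definition is undated and its conditions are cumulative. If status at randomization was intended, the text should say so.

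A second reply is that late ineligibility is normally handled in a fuller protocol or SAP. That would answer a gap. Here the definitions are stated, and stated too narrowly.

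A reader might infer more than the text supports:

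- **That codes are issued before eligibility is checked.** They are not. Both sections require eligibility first. What remains is that one places screening within the baseline visit and the other names that visit after the code.
- **That poor adherence could be relabelled as ineligibility.** The criterion reads "Patient who, in the view of the attending physician, will not comply with treatment and/or scheduled visits". This is a forward-looking judgement at screening. Actual missed treatments and visits are dealt with in the per-protocol sample only.
- **That the KOH cure rate would be inflated.** That needs removals that differ by arm in one particular way. The attending pediatrician is blinded, although irritation could hint at allocation, and removal at equal rates leaves the contrast almost unchanged.
- **That ineligible children are at greater risk of harm from KOH.** The article does not say so.

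**Conclusion.** The point holds for the sample definitions. As written, a treated child found to breach a criterion is in none of the three analysed samples, so that child's adverse events have no denominator and ITT membership is not determined by randomization. The size cannot be fixed from the documents: the number of such children and the direction of any bias are unknown, and every count and rate above other than the plan's own inputs is an assumption. One or two children would still matter in arms of 20, chiefly for safety reporting and the integrity of the randomized comparison, with little effect on power. The sequence issue is secondary: two accounts of the baseline visit need reconciling, and neither shows randomization ahead of eligibility. The definitions should be corrected, but nothing in the text shows that a biased result was planned or is likely.

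**What to change.** 1. Define the safety sample as every child who received at least one application of study solution, whatever later emerges about eligibility. This wording also removes any doubt about whether the parenthesis on follow-up visits is a condition of entry.
2. Remove the eligibility condition from the ITT sample.
3. Add to the per-protocol violations an eligibility breach established from facts dated before the code was assigned. This addition is needed because none of the three current violations would exclude such a child once ITT is widened.
4. Reconcile section 1.1 (Summary of trial design) with section 1.6, so that both give the same order for screening, baseline recording and assignment of the code.

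The cost is the rewording of three definitions and one statement of sequence, with no extra patients or data. The small downside is that a few ineligible children stay in ITT and may dilute the effect slightly; the amended per-protocol sample would show the result without them.
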